### Randomization and blinding

2.6

A software called SPSS Statistics Version 17.0 (IBM Corp., Armonk, New York) will be used to generate randomization sequence. The randomization sequence will be concealed and disseminated using opaque envelopes. Participants will be randomly divided into an intervention group and a control group in this way. In the progress of our study, evaluators, participants, and experimental researchers will be blinded. Unblinding is allowed to be performed only when the participant has an adverse reaction. The first time an adverse reaction occurs, the principal investigator will immediately assess the patient's condition and record in detail the time, place, and possible cause of the adverse reaction in Case Report Forms. In this experiment, the drug distribution managers and data analysis experts will not be directly involved in the process of the study and intentional analysis will be applied to the unblinding participants.

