### Study design and settings

2.3

The study will be a double-blind, randomized controlled trial. It will be carried out in the Hospital of Chengdu University of Traditional Chinese Medicine. The study protocol follows the recommendations of the Standard Protocol Items for Randomized Trials and the Consolidated Standards of Reporting Trials Extension for CHM Formulas statemen.^[23,24]^ The author of this protocol will truthfully inform the participants of this experimental study, procedures, potential risks, and benefits. With their consent, they will sign an informed consent form and abid by the schedule represented in Fig. 1. It is worth mentioning that participants can only participate in the study if they have fully read, agreed, and signed an informed consent form.

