#### Control group

3.2.1

As metformin is currently the first-line medication for T2DM, participants in this group will take 500 mg of metformin orally 3 times a day (if there is gastrointestinal discomfort, it can be taken during meals or 15 minutes after meals); the course of treatment is 3 months.

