#### Intervention group

3.2.2

Participants in this group will take the same dose of metformin as the control group. In addition, they will take SC. In this study, SC was provided by the Hospital of Chengdu University of traditional Chinese Medicine. The composition of the drug is: Ginseng, Rehmannia Glutinosa, Aspart Asparagus, Black Plum, Cinnamon, Coptis. The formula is made into powder according to the compatible dosage. Each dose is 88.5 g, divided into 3 parts, each part is taken with 200 mL of boiling water and taken 20 minutes before 3 meals. No other drugs are used during treatment period. It is worth mentioning that the change of conditions should be closely monitored at this time so as to control the deterioration of conditions in time.

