### Secondary outcome measures

4.2

We will use mean blood glucose (MBG), largest amplitude of glycemic excursions (LAGE), postprandial glycemic excursions (PPGE), glycated hemoglobin as the secondary outcome measures. In the whole process, we will also collect the following indicators:

(1)Total effective rate; the judgement of effectiveness takes into account the improvement of examination indicators and the relief of clinical symptoms.(2)Hyperglycemia or hypoglycemia that may occur during the study.(3)Have any adverse effects of medication throughout the process.

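### Participants and experimental researchers are declared blinded, but the regimens described (metformin alone against metformin plus a herbal powder, with no placebo) do not allow it

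*Protocol article*

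**What the plan says.** Section 2.3 (Study design and settings) sets the label: "The study will be a double-blind, randomized controlled trial". Section 2.6 (Randomization and blinding) says who is covered: "In the progress of our study, evaluators, participants, and experimental researchers will be blinded". It adds a rule that presupposes a working blind: "Unblinding is allowed to be performed only when the participant has an adverse reaction". The same section keeps the drug distribution managers and the data analysts out of the direct conduct of the study.

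Section 3.2.1 (Control group) gives the comparator: "participants in this group will take 500 mg of metformin orally 3 times a day". Section 3.2.2 (Intervention group) defines the other arm as an addition to it: "Participants in this group will take the same dose of metformin as the control group. In addition, they will take SC". SC is a powder divided into three parts, and "each part is taken with 200 mL of boiling water and taken 20 minutes before 3 meals". The Method part of the Abstract describes the same comparison, conventional western medicine with or without SC. The readable text mentions no placebo, dummy powder or other masking of SC.

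**The concern.** Blinding participants requires that the two arms look alike to the person taking the treatment. Here one arm prepares and drinks a herbal powder three times a day and the other is described as receiving nothing in its place. The stated design property and the stated regimens therefore conflict.

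What is at stake differs by outcome:

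- **Symptoms.** Objective 2 in section 2.2 is improvement of diabetes symptoms. The TCM syndrome score (section 4.3) comes from questionnaires, and for the total effective rate (section 4.2) "the judgement of effectiveness takes into account the improvement of examination indicators and the relief of clinical symptoms". Someone who knows that they received the extra treatment may report more relief.
- **Adverse effects.** Reporting can also change when the participant knows the arm.
- **SDBG and CV.** These are calculated from finger-prick glucose profiles, so no rating is involved, but eating, exercise and adherence affect the readings.

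A reader who trusts the double-blind label would give the symptom and safety results more weight than the described design supports.

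**Working it through.** No arithmetic applies and the plan gives no figure to reproduce. The check sets the sections side by side.

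1. **Claim.** Sections 2.3 and 2.6: double-blind, with three parties blinded (evaluators, participants, experimental researchers).

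2. **What each arm takes.**

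| | Metformin | Powder before meals |
|---|---|---|
| Control (3.2.1) | 500 mg, 3 times a day | none described |
| Intervention (3.2.2) | same dose | SC, 3 parts a day, each with 200 mL of boiling water |

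The only described difference is SC, and the participant sees and tastes it.

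3. **Can each declared party be blind under these regimens?**
 - *Participants:* no. Section 2.3 says that they are told about the study and its procedures before consent. A participant who then drinks the powder, or is given none, can tell the arm.
 - *Experimental researchers:* not those who give or explain the treatment, since preparing and timing the powder has to be explained in one arm only. The article does not say which staff do this, so how many are affected is not known.
 - *Evaluators:* yes, if they are kept apart from treatment and participants do not disclose it.
 - *Data analysts* (kept apart in section 2.6, though not in its list of blinded parties): yes, if they work from coded data.

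4. **Is the control regimen merely abbreviated?** Section 3.2.1 gives drug, dose, frequency, advice on timing in case of stomach upset, and duration. Section 3.2.2 then defines the other arm as that regimen with SC added. A placebo would belong in 3.2.1 and is not there.

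5. **Either way, text must change.** If there is no placebo, sections 2.3 and 2.6 are wrong about participants and treating staff. If there is one, section 3.2.1 misdescribes the control arm.

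6. **Extent.** The question of whether the arm is known applies to 30 + 30 = 60 planned participants. How far this would shift any outcome cannot be calculated from the document.

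**The case against.** The strongest defence is that an article condenses a fuller protocol, that the flowchart in Fig. 1 is not readable here, and that a placebo may be described elsewhere. This properly limits the claim: what is shown is that no placebo is described, not that none exists. It does not remove the conflict, because the article spells out the control regimen and defines SC as the addition to it. The sentence in section 3.2.2, "No other drugs are used during treatment period", does not settle the matter. It stands in the intervention-group paragraph, and a placebo need not count as a drug.

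Three further objections stand and limit the point.

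- A reader might infer that the trial has no blinding at all and that the unblinding rule in section 2.6 is empty. The text does not support this. Evaluators and analysts can be blinded without a placebo, and the rule can still protect the evaluators' blinding.
- A reader might infer that every outcome is biased towards SC. That direction is plausible for symptom reports only. For SDBG and CV it is unknown: controls who know that they receive no extra treatment might tighten their diet, which would work against SC. Section 3.1 also gives all participants a 2-week lifestyle run-in to standardise diet and exercise, although this does not secure adherence over the 3 months that follow.
- The total effective rate does not rest on self-report alone, since it also uses examination indicators. Neither it nor the TCM score is a primary outcome.

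**Conclusion.** The point holds as an internal contradiction. With the regimens as written, blinding of participants and of staff who give or explain treatment cannot hold, while blinding of evaluators and analysts can. This must be corrected before the trial is reported as double-blind, because the label affects how the symptom and safety results are read.

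The exposure is greatest for the TCM questionnaire, the symptom part of the total effective rate and adverse-effect reports. It is indirect and of unknown direction for SDBG and CV. No size of bias can be given. The conclusion assumes that section 3.2.1 describes the control regimen completely. If a matching placebo is in use, the error lies in that section and the blinding claim may be sound. Lack of a placebo in an add-on trial is not in itself the fault found here; the fault is the claim of a blind that the described arms cannot deliver.

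**What to change.** Reconcile sections 2.3 and 2.6 with 3.2.1 and 3.2.2 in one of two ways.

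1. **If a matching placebo is used:** describe it in section 3.2.1, including how it is matched to SC, and keep the blinding claim.

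2. **If none is used:**
 - In sections 2.3 and 2.6 replace the double-blind label with open-label with blinded evaluators and analysts, and delete the claim that participants and experimental researchers are blinded.
 - Have SDBG, CV, LAGE and PPGE calculated and analysed by staff who see arm codes only.
 - Label the TCM symptom scores and the total effective rate as unblinded, supportive outcomes.
 - State conclusions as the effect of adding SC to metformin without placebo control.

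If a placebo is already in use, the first route costs only added text. The second costs a less favourable design label and minor data-coding work. Neither changes the sample size or the choice of primary outcomes.

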## Interventions

3

### Run-in period

3.1

According to the 2010 China Type 2 Diabetes Clinical Practice Guidelines,^[26]^ all participants will receive lifestyle interventions for 2 weeks, in order to standardize their diet and exercise therapy.

### SC intervention

3.2

#### Control group

3.2.1

As metformin is currently the first-line medication for T2DM, participants in this group will take 500 mg of metformin orally 3 times a day (if there is gastrointestinal discomfort, it can be taken during meals or 15 minutes after meals); the course of treatment is 3 months.

#### Intervention group

3.2.2

Participants in this group will take the same dose of metformin as the control group. In addition, they will take SC. In this study, SC was provided by the Hospital of Chengdu University of traditional Chinese Medicine. The composition of the drug is: Ginseng, Rehmannia Glutinosa, Aspart Asparagus, Black Plum, Cinnamon, Coptis. The formula is made into powder according to the compatible dosage. Each dose is 88.5 g, divided into 3 parts, each part is taken with 200 mL of boiling water and taken 20 minutes before 3 meals. No other drugs are used during treatment period. It is worth mentioning that the change of conditions should be closely monitored at this time so as to control the deterioration of conditions in time.

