## Outcome measures

4

We will collect the characteristics of the 2 groups of participants at baseline and after the intervention, such as age, sex, physical examination, biochemical indicators, and other data (twice in total). The primary outcome indicators and secondary outcome indicators are measured and calculated at baseline, the first month, the second month, and the third month, respectively. (Four times in total.)

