### Conditions for suspension and withdrawal of clinical trials

4.4

The research staff of this clinical trial should record in detail the reasons why the participant proposed to withdraw from the clinical trial or the subjects’ reluctance to continue the clinical trial, and record in detail the evaluation indicators at the time of drug withdrawal. In addition, the reason for discontinuing the trial and its relationship with the clinical trial should be clearly documented. When the participants have the following conditions, we will suspend and withdraw clinical trials.

(1)People who quit the study themselves.(2)People who can’t insist on treatment.(3)In case of allergic reaction or serious adverse reaction during the test, the test shall be suspended. The ethics committee will assess any correlation between the adverse event and the intervention, and make a decision on whether the study should proceed.(4)Those who did not follow the plan strictly.(5)People who joined other clinical trials in the course of this experiment.

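### Another drug given for worsening glycaemia can lead to withdrawal under 4.4(4), so later values may be lost for a reason tied to the primary outcomes

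*Protocol article*

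**What the plan says.** Four statements in the protocol article bear on this.

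- Section 3.2.2 (Intervention group) sets the drug rule: "No other drugs are used during treatment period". It then adds that "the change of conditions should be closely monitored at this time so as to control the deterioration of conditions in time". It names no means of control and no permitted drug.
- Section 4.4 opens its list with "When the participants have the following conditions, we will suspend and withdraw clinical trials". Item (4) reads "Those who did not follow the plan strictly". Treatment for deterioration is not excepted.
- Before that list, 4.4 asks staff, for participants who propose to withdraw or are reluctant to continue, to "record in detail the evaluation indicators at the time of drug withdrawal".
- Section 4 plans the primary and secondary outcomes to be "measured and calculated at baseline, the first month, the second month, and the third month". Section 4.2 expects glycaemic events, since it collects "Hyperglycemia or hypoglycemia that may occur during the study".

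The only wording that resembles intention to treat is in 2.6. It covers unblinded participants, and unblinding is allowed only after an adverse reaction.

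**The concern.** The drug rule and the instruction to control deterioration pull against each other. If staff add a drug for a participant whose glucose is worsening, they break the rule in 3.2.2, and that participant then fits 4.4(4). What triggers removal is glycaemic control, and both primary outcomes are computed from blood glucose. Withdrawal could therefore be related to the outcome rather than random.

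An analysis plan can choose the analysis set and the method for missing data, but it cannot supply month-3 values that were not measured. If the missing values come mainly from participants doing badly, the month-3 comparison is between selected groups. In a trial of 30 per arm, a few such losses can matter.

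**Working it through.** **Reading the text.** The chain has three links.

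1. Deterioration is treated with another drug. This is inferred: 3.2.2 asks for control and does not say how.
2. Giving that drug counts as not following the plan strictly. This follows from the plain words of 3.2.2 and 4.4(4).
3. Measurement stops after withdrawal. This too is inferred: 4.4 mentions indicators at drug withdrawal and is silent on later visits.

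The text therefore supports *can be withdrawn* and *may be lost*, and no more.

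**Inputs.** The document gives no rate of added treatment, so the size can only be illustrated.

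- From 2.5: SDs of 0.28 (SC) and 0.35 (control) for SDBG, 0.31 and 0.67 for CV; 30 per arm; 20% dropout.
- Assumed: 0.39 and 0.41 are between-group differences. For SDBG this agrees with the stated 14 per group: (1.960 + 1.282)² × (0.28² + 0.35²) / 0.39² = 10.51 × 0.2009 / 0.1521 = 13.9. For CV the same formula gives 10.51 × 0.5450 / 0.1681 = 34.1, so 35 rather than the stated 25. That is a separate matter, and 0.41 remains an assumption here.
- Assumed: k = 3 or 6 of 30 withdrawn per arm, namely those worst on a score that has correlation ρ with the month-3 value; normal outcomes; pooled t test, two-sided 0.05; power counts results in favour of SC. Note that 6 of 30 equals the planned 20% dropout.

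**Shift when the rule applies in both arms.** Removing the k highest of 30 standard normal values lowers the mean of the rest by h = 0.186 (k = 3) or 0.338 (k = 6). Hence

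shift against SC = ρ × h × (SD control − SD SC).

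The SD difference is 0.35 − 0.28 = 0.07 for SDBG and 0.67 − 0.31 = 0.36 for CV.

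| ρ | SDBG, k = 3 / 6 | CV, k = 3 / 6 |
|---|---|---|
| 1 | 0.013 / 0.024 | 0.067 / 0.122 |
| 0.5 | 0.007 / 0.012 | 0.033 / 0.061 |
| 0.2 | 0.003 / 0.005 | 0.013 / 0.024 |
| −0.3 | −0.004 / −0.007 | −0.020 / −0.037 |

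A negative entry favours SC.

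**Power, by simulation (40,000 trials per setting).** SDBG stays at or above 98%. For CV:

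- no loss: 85%
- random loss of 3 / 6 per arm: 81% / 76%
- ρ = 0.2: 79% / 71%
- ρ = 0.5 to 1: 76% / 65% to 66%

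The plan already allows for 20% dropout, so the fair contrast at 6 per arm is 76% against 65% to 66%. The drop from 85% is not the right measure.

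**Same people kept and measured.** Suppose the added drug lowers their CV by 0.2 to 0.41. With ρ = 0.5 to 1, CV power is 86% to 91% with no shift. The excess over 85% arises because the assumed drug effect pulls in the upper control tail; with ρ = 0 it is 82% to 84%.

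**A case less favourable to keeping them.** Take one common cut-off passed by 10% to 20% of controls and almost no SC participants, with ρ = 0.5 to 1. If they are kept and treated, the CV difference of 0.41 is diluted to between 0.39 and 0.33, with power 71% to 84%. If they are withdrawn, it falls to between 0.34 and 0.18, with power 72% to 36%. In each matched setting, keeping them gives the higher power.

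**The case against.** The strongest reply is that two links are inferred. Control of deterioration could mean stopping SC or tightening diet and exercise. Item (4) sits beside items on participants who cannot keep to treatment or join other trials, so it may be aimed at participant non-adherence. The recording sentence in 4.4 comes before the list, concerns people who ask to leave, and does not say that later visits stop. A rescue rule and follow-up after discontinuation are also details that an article often leaves to the full protocol.

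Much of this stands, and it limits the point to what can happen. It does not remove the point, because the drug ban and the withdrawal condition are stated rules that conflict with the instruction beside them.

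The objection to the size also stands. The rates and correlations have no source. Added treatment may follow glucose level rather than variability. If CV is SD divided by mean (the formula table is not shown), sustained hyperglycaemia raises the denominator, so a small or negative correlation is possible.

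A reader might infer three stronger claims, none of which the article supports:

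- *Withdrawn participants are excluded from the analysis.* The article does not say so.
- *The error works against SC.* That needs a positive correlation as well as the larger control SD.
- *Only SC participants can be removed, which inflates the benefit.* The ban stands in the SC section but names no arm. Section 2.3 says "The study will be a double-blind, randomized controlled trial", and blinded researchers could hardly enforce a one-arm ban, so a rule for both arms is the more plausible reading. Even under the one-arm reading, control participants could be treated and kept. With no true effect and an assumed drop of 0.2 to 0.5 in SDBG, the shift runs from 0.055 in favour of SC to 0.053 against, so its direction is not established.

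**Conclusion.** The point holds as a conflict in the stated rules: a participant treated for deterioration can be withdrawn, and values up to month 3 may then be missing for a reason related to the primary outcomes. How often this would happen, how large the bias would be and which arm it would favour cannot be known from the document.

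Under assumed losses of 3 to 6 of 30 per arm in both arms, SDBG is hardly touched. CV is more exposed because its planning SDs differ widely between arms. Its shift runs from 0.122 against SC at perfect correlation, through 0.013 to 0.024 against at 0.2, to 0.020 to 0.037 in favour at −0.3. At 6 per arm and correlation 0.5 to 1, the power cost beyond random loss is about 10 to 11 percentage points. The change is worth making because it is cheap and unmeasured values cannot be restored later.

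**What to change.** - In 3.2, state one co-medication rule that covers both arms.
- In 4.4, say that treatment for deterioration, or stopping study drug, does not end follow-up. Separate stopping study drug from leaving the study.
- Measure these participants at every planned visit through month 3 and analyse them as randomised.
- Report added drugs by arm beside the primary result.

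The cost is a wording amendment to 3.2 and 4.4 and one more case report form page. The statistical price is some dilution of the SC effect by added treatment: in the less favourable assumed case, a CV difference of 0.41 becomes 0.39 to 0.33.

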## Outcome measures

4

We will collect the characteristics of the 2 groups of participants at baseline and after the intervention, such as age, sex, physical examination, biochemical indicators, and other data (twice in total). The primary outcome indicators and secondary outcome indicators are measured and calculated at baseline, the first month, the second month, and the third month, respectively. (Four times in total.)

### Primary outcome measures

4.1

We will use the SDBG and CV as the main outcome measures.

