### Sample size calculation

2.5

The study used SBDG and CV as the main outcome indicators. In the preliminary experiment, the mean value of SBDG between the 2 groups was 0.39, and the standard deviations of treatment group and control group were 0.28 and 0.35 respectively. On the other hand, the mean value of CV between the 2 groups was 0.41, and the standard deviations of treatment group and control group were 0.31 and 0.67 respectively. Set *α* to 0.05 and *β* to 0.1. The sample sizes calculated using PASS 11 software were 14 and 25, respectively. In order to ensure statistically meaningful results, considering the 20% dropout rate, and according to the formula of n ^ = n/(1–f), the total number of studies was determined to be 60 cases, 30 cases per group.

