### Efficacy evaluation

4.3

By calculating the SDBG and CV of the participants at baseline, the first month, the second month, and the third month, the efficacy will be evaluated (Table 2). At the same time, we will also evaluate MBG, LAGE, and PPGE, glycated hemoglobin as secondary efficacy evaluations. We will use a simple method is to get blood sugar and calculate the above indicators which is finger-prick measurements within a specific period, 7-point profiles (7 am, 9 am, 11 am, 1 pm, 5 pm, 7 pm, and 9 pm). Despite the lack of nocturnal blood glucose measurements, the SDBG can be an appropriate data even in data sets in which glucose values do not follow a Gaussian distribution, because it has a near linear relation with the interquartile range.^[27,28]^ In addition, we will measure the following indicators at baseline and at the end of the experiment: blood pressure, fasting plasma glucose, total cholesterol, low density lipoprotein cholesterol, high density lipoprotein cholesterol, triglycerides, advanced glycation end products, and changes in the scores of TCM syndromes measured by questionnaires.

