### Statistical analysis

4.5

Data processing uses SPSS statistical software version 17.0 (IBM Corporation). Normally distributed variables are expressed as mean and standard deviation; non-normally distributed variables are expressed as median and quartile range. Normally distributed variables between groups using independent sample *t* test, rather than the normal difference variables using Mann–Whitney *U* test. In the comparison group, paired *t* test variables were normally distributed, non-normally distributed variables the Wilcoxon rank sum test. *P* < .05 was considered a statistically significant difference. Study figures were created using SigmaPlot (Systat Software Inc.).

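### Two equal main outcomes, three post-baseline months and a blanket P < .05, with no primary month and no success rule, leave the error rate of the primary claim unfixed and probably above 5%

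*Protocol article*

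**What the plan says.** All references are to the protocol article.

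- **Outcomes.** Section 4.1: "We will use the SDBG and CV as the main outcome measures". Section 2.5 repeats it ("The study used SBDG and CV as the main outcome indicators") and sizes each outcome separately, with alpha 0.05 and beta 0.1. Objective 1 in section 2.2 also puts the two on an equal footing.
- **Times.** Section 4 has the primary and secondary outcomes "measured and calculated at baseline, the first month, the second month, and the third month, respectively". Section 4.3 bases the efficacy evaluation on "calculating the SDBG and CV of the participants at baseline, the first month, the second month, and the third month". No month is singled out. Section 3.2.1 sets the course of treatment at 3 months.
- **Tests.** Section 4.5 gives for group comparisons: "Normally distributed variables between groups using independent sample *t* test", with Mann-Whitney otherwise. No longitudinal model is described.
- **Threshold.** In section 4.5, P below .05 "was considered a statistically significant difference", for every comparison alike.

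**The concern.** A primary endpoint is complete only when the variable, the time point and the condition for success are all fixed. Here there are two variables, three candidate months and a single-test threshold. Nothing reduces the possible comparisons to one decision. The natural reading of sections 4, 4.3 and 4.5 together gives 2 x 3 = 6 between-group comparisons on main outcomes, each at the full 5%.

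The trial's central claim is that SC reduces glycaemic variability. If one significant result among several can be reported as confirming it, the nominal 5% no longer describes the risk of a false claim. Choosing the outcome or the month after seeing the data cannot restore it.

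**Working it through.** **1. The protocol's own figures (section 2.5).** I read 0.39 (SDBG) and 0.41 (CV) as between-group differences and alpha as two-sided; the text states neither outright. The formula is n per group = (s1² + s2²)(1.960 + 1.282)² / d².

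- SDBG: (0.28² + 0.35²) x 10.51 / 0.39² = 0.2009 x 10.51 / 0.1521 = 13.9, so 14. This reproduces the protocol.
- CV: (0.31² + 0.67²) x 10.51 / 0.41² = 0.5450 x 10.51 / 0.1681 = 34.1, so 35. The protocol gives 25, which is not reproduced. That is a separate matter, but it bears on the power figures in step 5.

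**2. Either outcome, one month.** If the tests were independent: 1 - 0.95² = 9.75%. With correlation between the two test statistics: 9.0% at 0.5, 7.9% at 0.8, 7.0% at 0.9.

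**3. Either outcome, any of three months.** If all six tests were independent: 1 - 0.95⁶ = 26.5%. Independence is not credible here, because SDBG and CV are computed from the same 7-point profiles and the same patients are measured each month. I therefore simulated six correlated normal test statistics under no effect (400,000 draws, two-sided 0.05 each). The correlations are assumptions.

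| Between outcomes | Between months | At least one false positive |
|---|---|---|
| 0.5 | 0.3 | 23.8% |
| 0.5 | 0.5 | 21.9% |
| 0.7 | 0.5 | 20.3% |
| 0.8 | 0.5 | 18.9% |
| 0.7 | 0.7 | 17.6% |
| 0.9 | 0.7 | 15.0% |
| 0.9 | 0.9 | 11.6% |
| 0.95 | 0.9 | 10.6% |

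These rates count false positives in either direction. Those favouring SC alone are about half: about 12% in the first row and 5.8% at 0.9/0.9, against a nominal 2.5%.

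**4. Both outcomes required.** At one named month, testing each at 0.05 keeps the error at or below 5%. With no effect on either outcome, simulation gives 1-3% at month 3. If both must succeed at the same month but any of the three months will do, it gives 3-7%.

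**5. Power under a defined rule.** Completers per group: 30 x (1 - 0.2) = 24. For the t test with 46 degrees of freedom, the noncentrality is d / √((s1² + s2²)/24).

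- SDBG: 0.39 / √(0.2009/24) = 4.26. Power is 98.7% at 0.05 and 97% at 0.025.
- CV: 0.41 / √(0.5450/24) = 2.72. Power is 76% at 0.05 and 66% at 0.025.

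**The case against.** **Month-by-month testing is never stated in so many words.** Section 4 gives a measurement schedule and section 4.5 a generic list of tests. A single comparison at the end of the 3-month course also fits the text. This stands, and it is why the size is given separately for each reading. It does not remove the problem: with either outcome sufficient at month 3 alone, the error is still 7-10%.

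**The trial may be meant to require both outcomes.** The final size rests on the larger of the two requirements (25, not 14), which suits a design where both must succeed; a full 0.05 for each would then be correct. So the separate alphas in section 2.5 are not in themselves evidence of a fault. But the protocol does not state this rule, and without a named month it would not settle the error rate.

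**Multiplicity often sits in an analysis plan, and this is a condensed article.** That is fair for the details of alpha allocation. The time point and success rule, however, define the primary endpoint. Section 4.1 defines it without either, and section 4.5 states a threshold for every comparison that a later plan would have to override.

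**Stronger readings that do not hold.**

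- A reader might infer a false-positive risk as high as 26%. That needs six independent tests.
- A reader might take 15% as the minimum. Higher correlations give 11-12% or less.
- A reader might infer that requiring both outcomes is what pulls power from 90% to about 75%. CV alone has only 76% power with 24 per group, so the shortfall lies in the CV sample size, not in multiplicity.

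**Conclusion.** The point holds in limited form. The protocol fixes two equal main outcomes, three post-baseline evaluations and one unadjusted threshold, and it leaves open which result counts as success. The two-sided chance of at least one false-positive primary result is about 7-10% if either outcome at month 3 suffices, and roughly 11-24% if any month counts. Both ranges rest on assumed correlations. Among rules that keep both outcomes primary with each tested at 0.05, only requiring both at one named month avoids inflation, and the text does not state it. The abstract's wording about exploring effects does not change this, since section 2.1 sets a directional hypothesis and section 2.5 sizes the trial for formal tests.

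**What to change.** Amend sections 4.1 and 4.5, and the registry entry to match, before the data are analysed:

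- Name month 3, the end of the treatment course, as the primary time point.
- Fix one success rule. For example: SDBG at month 3 at two-sided 0.05; CV at month 3 at 0.05 only if SDBG is significant.
- Report months 1 and 2 as supportive, as estimates with 95% confidence intervals.

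In section 2.5, keep 60 patients and state that 24 completers per group give about 98.7% power for SDBG and about 76% for CV on the stated inputs. Do not re-base the size on SDBG alone: 14 / (1 - 0.2) = 17.5, so 18 per group or 36 in total, which would no longer explain 60.

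The cost is a short amendment, with no added patients or visits. The real downside is that CV loses the equal status given in objective 1. If equal status matters more, test each outcome at month 3 at 0.025; power is then about 97% for SDBG and 66% for CV. Requiring both at 0.05 at month 3 would also control error, but power for the joint claim could not exceed CV's 76%.
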